## Abstract

**Clinical trial registration:**

Clinicaltrials.gov, NCT05568953.

## Introduction

Outbreaks of emerging and re-emerging viruses from animal reservoirs continue to plague mankind. In the past 20 years alone, at least eight viruses have emerged from zoonotic sources to cause epidemics and pandemics, the majority of which have no effective vaccines. Vaccine development is a costly endeavor, with many failed candidates that never achieve licensure. As clearly evidenced by the coronavirus disease 2019 (COVID-19) pandemic, the public health and socio-economic impact of viral outbreaks can be devastating, but can be dramatically reversed with mass vaccination. This further emphasizes the critical need to develop safe and effective viral vaccines in a timely and cost-effective manner.

The selection of vaccine candidates for clinical use is best guided by well-defined correlates of protection (CoP), i.e. an immune response that is responsible for, even if only in part, and statistically interrelated with protection (1). To date, vaccine development has relied heavily on measuring vaccine-induced antibody levels, a component of humoral immunity, as a correlate of protection. Humoral immunity, however, is only one arm of the overall host immune response to infection (2). Viral infection also elicits a cellular immune response, driven primarily by helper and cytotoxic T cells (3). Virus-specific memory T cells that develop following infection or immunization can be rapidly recalled during re-infection to aid antibody production (helper CD4+ T cells), and directly kill virus-infected cells (cytotoxic CD8+ T cells) (4, 5). Thus, while antibodies can prevent infection, T cells play an equally important role in reducing the total viral burden that drives inflammation and severe disease pathogenesis.

Indeed, the importance and protective role of T cell immunity has been clearly demonstrated in the context of flaviviral infections. Stronger and more polyfunctional antigen-specific T cell responses have been found in individuals with HLA alleles associated with a reduced susceptibility to severe dengue (6, 7), while asymptomatic dengue virus (DENV) infection has been associated with higher levels of cytokine-secreting T cells compared to symptomatic infection (8). The importance of T cell immunity has also been demonstrated in the context of dengue vaccine development. CYD-TDV, the first dengue vaccine to be licensed for use, is a live-attenuated vaccine comprising the structural pre-membrane and envelope genes of the four dengue serotypes with the non-structural and capsid genes of the live-attenuated yellow fever vaccine YF17D. Most of the CD8+ epitopes reside on the DENV non-structural proteins (9), which CYD-TDV does not contain, resulting in a limited DENV-specific T cell response. This likely contributed to the lacklustre efficacy observed with CYD-TDV in phase III trials, especially against DENV-1 and -2, despite robust levels of neutralizing antibodies (10, 11). In contrast, YF17D vaccine elicits a broad and polyfunctional yellow-fever specific T-cell response, demonstrating excellent efficacy against yellow fever, with a single dose conferring lifelong immunity (12).

Moving forward, it is thus crucial that future vaccine development efforts take into account the importance of T cell immunity in determining vaccine efficacy, and not focus solely on neutralizing antibody levels as a correlate of protection, as is currently often currently the case. Defining a minimum threshold of T-cell immunity, both in terms of frequency and functionality, would thus be critical in order to develop and select effective vaccines for the future.

## Hypothesis and objectives

The overall goal of this study is to define a minimum quantitative threshold of T cells induced by vaccination needed to control subsequent infection, independent of antibodies. We will conduct an experimental study in healthy adult volunteers, leveraging on the immunogenic properties of the licensed live-attenuated yellow fever (YF17D; STAMARIL^®^, Sanofi Pasteur) and chimeric Japanese encephalitis-YF17D (JE-YF17D; IMOJEV^®^, Sanofi Pasteur) vaccines. These vaccines contain the same genomic YF17D backbone (13, 14): vaccination with either vaccine would likely produce T cell responses that, like other flaviviruses, are preferentially directed against the non-structural proteins encoded in their shared genomic backbone, and hence would cross-protect against each other (**Figure 1**). YF17D and JE-YF17D, however, encode different structural pre-membrane (prM) and envelope (E) proteins: vaccination with either would produce neutralizing antibodies protective only against that virus (15). Moreover, YF17D and JE-YF17D vaccination induce different levels of infection as determined by vaccine RNAemia (16, 17), and expectedly differing levels of innate immune responses, allowing us to evaluate how RNAemia and innate immune profile shapes T cell response. The properties of these two live-attenuated vaccines thus provide a unique opportunity to differentiate the role of T cell immunity from humoral immunity in controlling viral infection. In addition, we will also use the licensed inactivated Japanese Encephalitis virus (JEV; IXIARO^®^, Valneva) vaccine to control for the effects of cross-reactive anti-flaviviral antibodies, although we have not observed suppression of YF17D RNAemia from inactivated JEV vaccination (16). Overall, we hypothesize that a high CD4+ and CD8+ T cell response will reduce RNAemia upon challenge with a structurally heterologous virus, and correspondingly result in reduced magnitude of host response to challenge infection. The specific objectives of the study are as follows:

**Figure 1 f1:**
[figure not shown]
Schematic representation of the genome of YF17D and chimeric JE-YF17D vaccines. JE virus prM and E genes (shown in red) have replaced those of YF17D in the chimeric virus.

### Primary objective

1. To compare, after challenge with a structurally heterologous vaccine (i.e. JE-YF17D or YF17D), the differences in RNAemia levels (as measured by RT-qPCR) between healthy adults who received primary vaccination with either YF17D vaccine, chimeric JE-YF17D vaccine, or inactivated JEV vaccine.

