### Study design

56 subjects will be randomized into 1 of 2 arms (Arm 1 and Arm 2) in a 1:1 ratio. These two arms will be double-blinded. Subjects in Arm 1 will receive JE-YF17D vaccine (IMOJEV^®^, Sanofi Pasteur) on Day 0, followed by YF17D vaccine (STAMARIL^®^, Sanofi Pasteur) on Day 28. Subjects in Arm 2 will receive YF17D vaccine on Day 0 followed by JE-YF17D vaccine on Day 28. A separate non-randomized non-blinded cohort of 14 subjects will be recruited into Arm 3. Subjects in Arm 3 will receive inactivated JEV vaccine (IXIARO^®^, Valneva) on Day 0 followed by YF17D vaccine on Day 28. **Table 1** summarizes the study design.

**Table 1 T1:** Study design.

Arms	Vaccination schedule	
	1^st^ vaccination (Day 0)	2^nd^ vaccination (Day 28)
Arm 1* (n=28)	JE-YF17D vaccine (IMOJEV^®^, Sanofi Pasteur)	YF17D vaccine (STAMARIL^®^, Sanofi Pasteur)
Arm 2* (n=28)	YF17D vaccine (STAMARIL^®^, Sanofi Pasteur)	JE-YF17D vaccine (IMOJEV^®^, Sanofi Pasteur)
Arm 3** (n=14)	Inactivated JEV vaccine (IXIARO^®^, Valneva)	YF17D vaccine (STAMARIL^®^, Sanofi Pasteur)

*Subjects (n=56) will be randomized in a double-blind manner to either Arms 1 or 2. **A separate cohort (n=14) will be recruited into Arm 3 in a non-randomized, single arm, open label design.

The rationale for these three study arms is as follows: Arm 1 will show the impact of a lower level of RNAemia induced by JE-YF17D vaccination (as compared to YF17D vaccination), and the resultant lower levels of virus-specific CD4+ and CD8+ T cells, would have on YF17D infection. In contrast, YF17D vaccination in Arm 2 would produce higher levels of RNAemia (as compared to JE-YF17D vaccination), and in turn higher levels of virus-specific T cells, thus likely resulting in greater suppression of JE-YF17D infection. The first vaccination in Arms 1 and 2 would provide the RNAemia response in the absence of virus-specific T cells, which would serve as a reference point to interpret the outcome of the second vaccination. For example, the level of suppression of JE-YF17D RNAemia will be the difference in RNAemia levels between subjects who received JE-YF17D as a second vaccination (Arm 2) compared to those who received it as a first vaccination (Arm 1), and similarly for YF17D vaccine. Arm 3 will serve as the control arm, as vaccination with inactivated JE vaccine should not produce any YF17D-specific T cell response.

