### Sample size calculation

To detect an effect size of 0.8 SD in mean RNAemia level on log (10) scale between the first and second dose with the same vaccine – first dose of YF17D will be analysed against those who received YF17D after JE-YF17D and vice versa – a sample size of 25 per group will provide 80% power at a 5% two-sided type 1 error rate. To allow for a drop-out rate of 10%, a total sample size of 28 per group for Arms 1 and 2 is targeted. For Arm 3, which is the control group, a sample size of 14 will be used.

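### As worded, the primary objective confounds priming with challenge virus in every comparison that involves Arm 2, and it is not the same-vaccine contrast that the protocol describes and powers

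*Protocol article*

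**What the plan says.** The Primary objective defines its groups by the first vaccine and its outcome by the period after the second. Its aim is "To compare, after challenge with a structurally heterologous vaccine (i.e. JE-YF17D or YF17D), the differences in RNAemia levels", and the groups set against each other are those primed with YF17D, with JE-YF17D and with the inactivated product.

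The Study design section gives the sequences:
- Arm 1 (randomised, n=28): "Subjects in Arm 1 will receive JE-YF17D vaccine (IMOJEV^®^, Sanofi Pasteur) on Day 0, followed by YF17D vaccine" on Day 28.
- Arm 2 (randomised, n=28): "Subjects in Arm 2 will receive YF17D vaccine on Day 0 followed by JE-YF17D vaccine on Day 28".
- Arm 3 (non-randomised, open label, n=14): "Subjects in Arm 3 will receive inactivated JEV vaccine (IXIARO^®^, Valneva) on Day 0 followed by YF17D vaccine on Day 28".

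The Hypothesis and objectives section states that "YF17D and JE-YF17D vaccination induce different levels of infection as determined by vaccine RNAemia". The rationale under Study design gives the direction: lower after JE-YF17D than after YF17D.

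Two sections set a different key comparison. In Study design, "the level of suppression of JE-YF17D RNAemia will be the difference in RNAemia levels between subjects who received JE-YF17D as a second vaccination" and those given it first, which means Arm 2 against Arm 1, with the same approach for YF17D. In Sample size calculation, "first dose of YF17D will be analysed against those who received YF17D after JE-YF17D and vice versa", with 0.8 SD on the log10 scale, 25 per group, 80% power and 5% two-sided error.

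**The concern.** The first vaccine and the challenge virus are tied together in this design. Arm 2 is the only arm challenged with JE-YF17D, so after Day 28 it has no comparator with the same virus. A difference between Arm 2 and either other arm is then the effect of priming plus the difference between the viruses, and post-challenge data alone cannot separate the two.

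The direction matters. The rationale predicts more T-cell suppression in Arm 2. It also expects JE-YF17D to give less RNAemia in people with no prior exposure. So Arm 2 could show the lower post-challenge level that the hypothesis predicts even if priming had the same effect in both arms, or none.

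The second issue is which test the power statement supports. The powered contrast uses RNAemia after the Day 0 dose as its reference. Those data fall before challenge, so they lie outside the primary objective as worded. If both statements stand, it is open which comparison is primary, and one candidate is biased toward success.

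**Working it through.** **1. The plan's own figure.** Inputs from Sample size calculation: difference 0.8 SD, two-sided 5%, 80% power.

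n per group = 2 × (1.960 + 0.842)² / 0.8² = 2 × 7.85 / 0.64 = 24.5, rounded up to 25. Normal-approximation power at 25 is 80.7%. With the t distribution, n is 25.5 and power at 25 is 79.1%. Allowing for 10% drop-out, 25 / 0.9 = 27.8, rounded up to 28. The stated 25 and 28 reproduce for the same-vaccine contrast.

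**2. What each comparison estimates.** Let Y and J be mean log10 RNAemia in unprimed people after YF17D and JE-YF17D, and D = Y − J. Let s1, s2 and s3 be the reductions that priming produces in Arms 1, 2 and 3.

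| Comparison | Expected difference | Depends on D? |
|---|---|---|
| Arm 1 minus Arm 2, after challenge | (Y − s1) − (J − s2) = D − s1 + s2 | yes |
| Arm 3 minus Arm 2, after challenge | (Y − s3) − (J − s2) = D − s3 + s2 | yes |
| Arm 3 minus Arm 1, after challenge | (Y − s3) − (Y − s1) = s1 − s3 | no |
| YF17D: Arm 2 after Day 0 minus Arm 1 after Day 28 | Y − (Y − s1) = s1 | no |
| JE-YF17D: Arm 1 after Day 0 minus Arm 2 after Day 28 | J − (J − s2) = s2 | no |

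The first three rows are the pairs within the objective as worded. The last two are the contrasts in Study design and Sample size calculation, and each isolates one suppression effect.

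**3. Size of the confounding.** The protocol says D is above zero but not how large it is, so D is an assumption here. Set s1 = s2 (equal suppression, including none), so that the expected Arm 1 versus Arm 2 difference is D alone. The table gives the probability of a significant two-sided 5% t-test at 25 per arm with a common SD.

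| D (SD, assumed) | P(significant) |
|---|---|
| 0 | 5% |
| 0.5 | 41% |
| 0.8 | 79% |
| 1.0 | 93% |

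**4. The one unconfounded pair within the objective.** For Arm 1 versus Arm 3 at 0.8 SD, t-test power is 66% with 28 versus 14 and 62% with 25 versus 13 (after about 10% drop-out). The differences detectable with 80% power are 0.94 and 0.98 SD. The protocol gives Arm 3 its 14 participants without a power statement.

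**5. Whether the samples support the powered contrasts.** Table 2 schedules blood RNAemia on Days 4, 7 and 10 and again on Days 32, 35 and 38, which are 4, 7 and 10 days after the second dose. Both same-vaccine contrasts can be formed at matching intervals.

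**The case against.** The strongest reply is that the protocol already says what it means. The Study design rationale makes the first vaccination the reference for the second and defines suppression within the same vaccine; the sample size follows suit. On that reading only the wording of the objective is loose. Much of this stands: the intended contrast is recoverable, and design, sampling and sample size all serve it. It does not dispose of the point. The primary objective states what the trial tests, and it states a different comparison. The literal reading is also not far-fetched, since the Vaccine RNAemia section presents the NS5 assay as allowing RNAemia from the two vaccines to be compared directly.

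A reader might infer more than the document supports:
- **That the trial plans to read lower RNAemia in Arm 2 as T-cell suppression.** No section says so. Where suppression is defined, the reference is unprimed recipients of the same vaccine.
- **That the whole primary objective is confounded.** Arm 1 versus Arm 3 shares the YF17D challenge. Its limits are lack of randomisation and low power.
- **That the sample size is wrong.** It reproduces for the contrast it names.
- **That secondary objectives 3 to 6 all fail in the same way.** The argument carries over to RNAemia duration (3). For symptoms (6), the analysis section already compares adverse events between first and challenge vaccination. Nothing here shows a fault in the T-cell and antibody objectives (4 and 5).
- **That the analysis section is at fault for naming no arms for the RNAemia tests.** A journal article may leave that to the full plan.

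**Conclusion.** The point holds as an internal contradiction. The primary objective as worded confounds priming with challenge virus in both comparisons that involve Arm 2, in the direction of the hypothesis, and it differs from the contrast that the protocol describes and powers. The 80% power statement does not apply to the objective as written.

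The 41%, 79% and 93% are conditional illustrations. They assume a virus difference of 0.5, 0.8 or 1.0 SD, equal or no suppression, a common SD and 25 per arm, and they fall to 5% if the viruses do not differ. They are not estimates of this trial's error rate. The structural result, that the difference contains D, needs only the arm sequences and the protocol's own statement that the two vaccines give different RNAemia.

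**What to change.** Reword the primary objective to the contrasts already present in Study design and Sample size calculation:
- YF17D: Arm 1 after Day 28 versus Arm 2 after Day 0.
- JE-YF17D: Arm 2 after Day 28 versus Arm 1 after Day 0.

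State Arm 1 versus Arm 3 (both YF17D after Day 28) as a supportive, non-randomised antibody-control comparison that the sample size does not power. State that post-challenge RNAemia in Arm 2 versus Arm 1 or Arm 3 is not used as a test of suppression.

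Apply the same contrasts to RNAemia duration (secondary objective 3). Align the symptom objective (6) with the first-versus-challenge comparison in the analysis section, and specify that it is made within the same vaccine.

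The cost is protocol text only. The existing schedule covers every contrast, and 25 evaluable and 28 enrolled per group stay as they are.

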### Secondary objectives

1. To compare the differences in magnitude and quality of the T cell response induced by primary JE-YF17D, YF17D, and inactivated JEV vaccination in healthy adults.2. To compare the differences in RNAemia levels after primary vaccination with either YF17D or JE-YF17D in healthy adults.3. To compare, after challenge with a structurally heterologous vaccine (i.e. JE-YF17D or YF17D), the differences in duration of RNAemia between healthy adults who received primary vaccination with either YF17D vaccine, chimeric JE-YF17D vaccine, or inactivated JEV vaccine.4. To compare, after challenge with a structurally heterologous vaccine (i.e. JE-YF17D or YF17D), the differences in magnitude and quality of T cell responses between healthy adults who received primary vaccination with either YF17D vaccine, chimeric JE-YF17D vaccine, or inactivated JEV vaccine.5. To compare, after challenge with a structurally heterologous vaccine (i.e. JE-YF17D or YF17D), the differences in neutralizing antibody titers between healthy adults who received primary vaccination with either YF17D vaccine, chimeric JE-YF17D vaccine, or inactivated JEV vaccine.6. To compare, after challenge with a structurally heterologous vaccine (i.e. JE-YF17D or YF17D), differences in systemic vaccine-related symptoms between healthy adults who received primary vaccination with either YF17D vaccine, chimeric JE-YF17D vaccine, or inactivated JEV vaccine.

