### Study visits and procedures

Informed written consent will be sought from subjects who fulfil criteria for enrolment. All consented subjects will undergo screening, which includes physical examination, full blood count, liver function test, and urinary pregnancy test (for female subjects of child-bearing potential). A flavivirus serostatus screen will also be performed using serum anti-dengue IgG as a surrogate marker for past flavivirus exposure.

**Table 2** shows the detailed study schedule. Study visits will occur on Day 0, 4, 7, 10, 14, 28, 29, 32, 35, 38, 42, 58. Subjects will receive vaccination on Day 0 and Day 28; at these visits blood sampling will be performed prior to vaccination. Subjects will undergo physical examination and research blood sampling at each study visit. Research blood samples will be collected at various time-points (see **Table 2**) for RNAemia measurement, T cell analysis, and antibody titer measurement. Urine samples will also be collected on Days 10, 14, 38 and 42 for urine viral RNA level measurement.

**Table 2 T2:** Study schedule.

	Screening (D-14 to D-1)	D0	D4 (+1d)	D7	D10 (+/- 1d)	D14 (+/- 2d)	D28	D29	D32 (+1d)	D35	D38 (+/- 1d)	D42 (+/- 2d)	D58 (+/- 3d)
**Informed consent**	x												
**Eligibility check**	x	x											
**Medical history and demographics**	x												
**Physical examination**	x	x	x	x	x	x	x	x	x	x	x	x	x
**Vital signs** ^a^	x	x	x	x	x	x	x	x	x	x	x	x	x
**DENV IgG ELISA**	x												
**FBC, Liver panel** ^b^	x												
**Urine pregnancy test** ^c^	x	x					x						
**Randomization** ^e^		x											
**Vaccination**		x					x						
**RNAemia level (NS5 PCR)**		x^d^	x	x	x		x^d^		x	x	x		
**T-cell studies**		x^d^		x	x	x	x^d^		x	x	x	x	x
**PRNT**		x^d^					x^d^						x
**Anti NS1 antibody**		x^d^	x	x	x		x^d^		x	x	x		x
**Urine NS5 PCR**					x	x					x	x	
**Adverse event monitoring**		x	x	x	x	x	x	x	x	x	x	x	x
**Concomitant medication history**		x	x	x	x	x	x	x	x	x	x	x	x

a Vital signs include temperature (oral or tympanic), blood pressure, pulse rate, and respiratory rate.

b FBC includes haemoglobin, red blood cell count, white blood cell count, haematocrit, platelet count, neutrophil, lymphocyte, monocyte, eosinophil, basophil. Liver panel includes total protein, albumin, total bilirubin, alkaline phosphatase, alanine aminotransferase, aspartate aminotransferase.

c For female subjects of child bearing potential only.

d Blood sampling will be performed before vaccine administration on Day 0 and Day 28.

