### Data and statistical analysis

Distributional diagnostic plots will be used to examine the shape of distributions of T-cell counts and RNAemia levels for each of the vaccines. Parametric or non-parametric procedures will be used to assess the differences in RNAemia levels T-cell counts, antibody titers and cytokine levels, as appropriate. The peak frequencies of activated CD4+ and CD8+ T cells will be compared using the student’s t-test. The duration of activated CD4+ and CD8+ T cell responses will be compared using area the curve (AUC), and the differences will be assessed using the Wilcoxon-rank-sum test. The level of antigen-specific cytokine production will be compared within each vaccine. Overall kinetics of cytokine production will be assessed for each time-point and compared with the baseline levels using a paired t-test. The peak cytokine production and AUC will be compared between both vaccines using the student’s t-test or Wilcoxon-rank-sum test, depending on whether the distribution is parametric or non-parametric, using the Shapiro-Wilk normality test or equivalent. The relationship between the activated T-cell frequencies and cytokine levels will be assessed using Spearman’s correlation analysis. To compare differences in RNAemia, both peak RNAemia and AUC will be compared using the student’s t-test or Wilcoxon-rank-sum test, depending on whether the distribution is parametric or non-parametric, using the Shapiro-Wilk normality test or equivalent, respectively.

The frequency and type of adverse events reported will first be analysed by determining the median and the interquartile ranges. Differences in frequencies of adverse events between the first and challenge vaccination will be analysed using 2x2 tables and chi square analysis or Fisher’s exact test, whichever is appropriate. Parametric or non-parametric procedures will be used to assess the differences in pre-challenge virus-specific T-cell counts among those with adverse events and those without.

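### Duration of RNAemia after challenge is a secondary objective, but blood PCR stops at post-dose Day 10, so anyone still positive on D38 has no observed end

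*Protocol article*

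**What the plan says.** Secondary objective 3 is to compare, after challenge with the structurally heterologous vaccine, "the differences in duration of RNAemia between healthy adults" who received YF17D, JE-YF17D or inactivated JEV as primary vaccination. It is a comparison between arms, all of them after challenge.

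In Table 2 (Study visits and procedures), the row beginning "RNAemia level (NS5 PCR" is marked at D0, D4, D7, D10, D28, D32, D35 and D38. It is blank at D14, D29, D42 and D58. On the two vaccination days, "Blood sampling will be performed before vaccine administration on Day 0 and Day 28", so D28 is both the last sample after the first dose and the baseline for challenge.

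Blood for T-cell studies is taken on D14, D42 and D58, and the text states that research blood is drawn at each study visit. Separately, "Urine samples will also be collected on Days 10, 14, 38 and 42 for urine viral RNA level measurement".

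Under Data and statistical analysis, "To compare differences in RNAemia, both peak RNAemia and AUC will be compared using the student’s t-test or Wilcoxon-rank-sum test". No integration window for the AUC is given. The first-dose against second-dose comparison is described for RNAemia level. Study design defines suppression of JE-YF17D as "the difference in RNAemia levels between subjects who received JE-YF17D as a second vaccination (Arm 2) compared to those who received it as a first" dose, with Arm 1 as the reference. Sample size calculation is built "To detect an effect size of 0.8 SD in mean RNAemia level on log (10) scale between the first and second dose with the same" product.

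**The concern.** A duration can be compared only if its end is observed or properly treated as unobserved. After challenge there are three blood PCR samples, and the last falls at post-dose Day 10. A subject who clears on Day 11 and one who clears three weeks later look alike.

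The loss need not be balanced. Study design states that inactivated JEV vaccination should induce no YF17D-specific T cells, so on the trial's reasoning Arm 3 should show the least suppression. Arm 1 receives the same YF17D challenge after a live vaccine with the shared backbone. If RNAemia outlasts Day 10 in anyone, it should do so more often in Arm 3. Scoring these subjects as ending at Day 10 shortens the longest durations in the control arm and shrinks the contrast that objective 3 is meant to show.

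**Working it through.** **1. The plan's own figure.** The article calculates nothing for duration. Its only computed figure is the sample size for RNAemia level: n = 2(1.96 + 0.84)²/0.8² ≈ 24.5, so 25 per group (power 80.7%), and 25/0.90 = 27.8, so 28. Both reproduce. The t-based version gives 25.5, so 26, with 79.1% power at 25, which is immaterial here. Nothing in this point changes that calculation.

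**2. Blood PCR by post-dose day (Table 2).**

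| Post-dose day | 0 | 4 | 7 | 10 | 14 | Later |
|---|---|---|---|---|---|---|
| First dose | D0 | D4 | D7 | D10 | D14: no PCR | D28 (pre-dose): PCR |
| Challenge | D28 | D32 | D35 | D38 | D42: no PCR | D58: no PCR |

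The visit windows match at Days 4 (+1 day), 10 (±1 day) and 14 (±2 days).

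**3. What can be recorded after challenge.** The last positive sample can fall only on post-dose Day 4, 7 or 10. A subject positive on Day 7 and negative on Day 10 has an end bracketed between those days. A subject positive on Day 10 has no upper bound.

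**4. Effect on the between-arm difference.** Let p be an arm's proportion still positive beyond Day 10 and m their mean excess in days. Capping at Day 10 lowers that arm's mean duration by p × m. The Arm 3 minus Arm 1 difference therefore shrinks by p₃m₃ − p₁m₁.

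The documents give neither p nor m. As an assumption, take m = 14 − 10 = 4 days in both arms (RNAemia lasting to Day 14). The loss is then 4 × (p₃ − p₁) days:

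- p₃ = p₁ = 0: no loss.
- p₃ − p₁ = 0.25: 1 day.
- p₃ − p₁ = 0.5: 2 days.
- p₃ − p₁ = 1: 4 days, the extreme.

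The direction is towards no difference whenever p₃m₃ exceeds p₁m₁, as the hypothesis would predict.

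**5. AUC (secondary point).** Over Days 0/4/7/10, identical curves give identical AUCs after either dose. They diverge only if D28 is added to the first-dose AUC. Using the trapezoid rule on assumed log10 values 0, 4, 4, 2 at Days 0/4/7/10 and 0 at Day 28:

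- Days 0–10: (0+4)/2×4 + (4+4)/2×3 + (4+2)/2×3 = 8 + 12 + 9 = 29.
- Days 10–28: (2+0)/2×18 = 18, total 47.
- Apparent reduction at challenge with no true effect: 1 − 29/47 = 38%.

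With 1 log at Day 10 the AUCs are 27.5 and 36.5, an apparent 25%. With a lower assumed curve (0, 2, 3, then V at Day 10), the apparent reduction is 9V/(16 + 10.5V): 0% at V = 0, 21% at 0.5, 34% at 1 and 49% at 2. These figures illustrate a calculation that the article does not say it will make.

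**The case against.** **There may be nothing to censor.** The documents contain no evidence that blood RNAemia persists past Day 10. Urine PCR on D14 and D42 shows interest in urinary RNA then, not an expectation of RNA in blood. This stands, and it is why the size cannot be stated.

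**The schedule is identical in every arm.** True, so sampling times themselves create no imbalance. It does not answer the point, because censoring depends on who is still positive, and that is what objective 3 compares.

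**The article condenses a fuller plan.** A statistical analysis plan may well say how censored durations and the AUC window are handled. For the AUC window this objection succeeds: its absence is ordinary detail, not an error. For duration it does not, because Table 2 fixes the samples and an analysis rule cannot add one.

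**The blood may not be usable.** T-cell work uses PBMCs or whole blood, and the article does not say that a plasma or serum aliquot is kept on D14 and D42. This is fair and belongs in the cost.

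Two stronger readings are tempting. A reader might infer that the D28 sample, which only the first dose has, distorts the duration comparison. It does not: objective 3 compares challenge with challenge, and nowhere does the article compare duration between first dose and challenge. Scored as time to last positive, a subject positive on Day 10 and negative on D28 still scores Day 10. A reader might also infer that the AUC necessarily favours suppression. That too is unsupported, since Days 0/4/7/10 are common to both doses and D28 reads naturally as the challenge baseline.

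**Conclusion.** The point holds as a limit on one secondary objective: RNAemia duration after challenge is right-censored at post-dose Day 10 in every arm and measured on a three-sample grid. If censoring is more frequent in the less suppressed arm, as the trial's hypothesis implies, the difference is compressed towards no effect. The size is unknown, and it is zero if all subjects are negative by Day 10. The day losses shown rest on an assumed 4-day excess and assumed proportions.

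Peak RNAemia is not called into question by this point, and the sample size is unaffected. The AUC remark is a precaution; the 38% and 25% are not estimates of bias in this trial. Overall this is an inexpensive improvement worth making, not a defect that invalidates the design.

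**What to change.** - **Sampling.** Add blood NS5 PCR at D42, so that challenge is followed to post-dose Day 14, and at D14, so that both doses share a 0/4/7/10/14 grid. In Table 2 only the RNAemia row changes.
- **Analysis of duration.** Treat a subject positive at the last scheduled sample as censored there, not as having cleared. The added sample moves the limit from Day 10 to Day 14 but does not abolish it, so this rule is needed in any case.
- **AUC.** For first dose against challenge, integrate over the same post-dose days. Keep the D28 pre-dose sample as the challenge baseline and as a check that first-vaccine RNA has cleared, because the NS5 assay detects both live vaccines.

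**Cost.** At most 70 × 2 = 140 extra PCRs (70 if only D42 is added), with no new visit because research blood is already drawn on those days. The sponsor must confirm that an aliquot suitable for RT-qPCR is kept at D14 and D42. The censoring and common-window rules cost nothing.
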